#### Randomisation

The randomisation process was conducted in each of the three hubs separately and in the presence of representatives from each village within that geographical area. The clusters in each area were listed in order of their population size. The four clusters with the largest populations were labelled “stratum 1”, the next four largest as “stratum 2”, and so on down to the four smallest size clusters (stratum 6). Two red and two yellow balls were put in an opaque cotton bag. The representatives from stratum 1 were called forward and each in turn blindly withdrew one ball without replacement. This process was repeated for the remaining five strata in turn to randomly designate 12 clusters as “red” and 12 as “yellow”. Finally, just one red and one yellow ball were placed in the bag and the eldest of the representatives present asked to blindly withdraw one ball. The clusters designated to the colour of the chosen ball were allocated to the intervention arm of the study and the clusters designated to the colour undrawn were allocated to the comparator arm of the study. The randomisation was thus stratified by geographical area and by population size. [name], a researcher not involved in the day-to-day running of the trial has, kept the final randomisation sequence and will only avail this to the other scientists at the end of trial.

### Identification, recruitment, and study procedures

The study processes were initially piloted in 10 villages [13] and refined, resulting in this final procedure. The village health team (VHT) member identifies potential participants and inquires whether they are interested in being enrolled in the study. Women may also be identified when presenting at antenatal clinics in hub facilities. The VHT notifies the research midwife about the potential participant. The research midwife visits the home and spends time with the woman explaining the study, what is involved, how long the woman and her baby are involved in the study and whether she is willing to give informed consent to participate. Each woman is told that once she has given her consent, she is free to withdraw from the study at any point and that the care and treatment of herself and her baby will not be affected. Should a woman withdraw from the study, the research team gently question her to attempt to ascertain the reason for her withdrawal from the study. The same is done for women who decline to enrol. No pressure is exerted should the woman be resistant to giving a reason, but feedback obtained from this interaction provides valuable feedback to the research team for approaching other women in the study.

Those in the intervention arm are given their supply of ABHR and trained fortnightly in its use by the ABHR trainer in a series of antenatal visits and reminder calls. Those in the control arm receive only a single recruitment visit antenatally in addition to standard antenatal care.

A VHT member (or the woman herself) is encouraged to inform the BabyGel midwives or hotline (calls are free of charge) when she has given birth and a research midwife visits within 48 h either at the participant’s home or at a health facility if the participant is still admitted. The same research midwife performs regular telephone calls and personal follow-up visits up to 12 weeks (trial completion).

The women are screened and recruited into the study at 34 weeks’ gestation. Gestational age is measured using an application on the midwives’ tablet or the obstetric ultrasound report if available or physical inspection. The women and their babies are followed for 3 months post-delivery. Therefore, participating women completing the follow-up period will be active in the study for approximately 20 weeks (± 2 weeks to account for inaccurate gestational age estimations).

Mothers are informed that, should their baby become sick for any reason, they can notify the study hotline, or beep/flash the BabyGel team or VHT, or come straight to the health facility. She and/or her baby are given free treatment and reimbursed travel expenses, a small daily subsistence payment is paid for any night that the mother and/or baby is admitted. Research midwives or VHTs refer babies with signs or symptoms of sickness to the nearby health facility or the Mbale Regional Referral Hospital Neonatal Unit (MRRH NNU) for specialised care. Study doctors are trained in the study protocol and to collect standardised data. They review the sick babies and either treat or transfer to MRRH NNU according to local guidelines and standard operating procedures.

As in the pilot study, all data are collected on REDCap software (Vanderbilt University, USA) installed on tablet computers and transferred to the Clinical Trial Unit (CTU) at the Liverpool School of Tropical Medicine through an encrypted transfer.

### Masking and code breaking

Although this is an open-label study, we attempt to mask the research midwives during the follow-up period (the trainers cannot be blinded as they deliver the ABHR to the participants). This is achieved by separating the research midwives and the trainers in two separate teams in different locations. Furthermore, we ask the study participants not to discuss their hand hygiene methods with the research midwives, and the mother is asked to keep the ABHR bottles out of sight of the research midwives on the day of the face-to-face visit. A research midwife informs the mother of the physical visit in advance to enable her to hide the ABHR if in an intervention cluster. Research midwives are encouraged to hand wash with soap and water in all clusters to minimise contamination. At the end of the 3-month follow-up, the closeout interview (which includes questions on the ABHR use and acceptability) is conducted by the trainer to prevent un-blinding of the research midwife to the village allocation.

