**Assessments:**														
***Baseline data collection***	X													
***Clinical, AE and SAE assessment, anthropometry***		X	X	X	X	X	X	X	X	X	X	X	X	
***Outcome assessment***						X	X	X	X	X	X	X	X	

^a^If still pregnant

^b^Telephone visit

A double-sided poster (Appendices 1 and 2) supplements the training, summarising the instructions in both a written and visual format, with one side specifying the correct antenatal and one the correct postnatal use of ABHR. The key message is that everyone should use ABHR “before touching the baby” (Appendix 3).

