### Participant and public involvement

We involved the women, families, and the public from the participating sites in the study design and continue to engage them in the conduct of the BabyGel trial. A participant and public involvement (PPI) steering team oversees all aspects of PPI in the project, including study design, trial information, protocol, and data collection tools or any other study specific documents, analysis, reporting, and dissemination. They also provide oversight for the conduct of PPI design workshops or group discussions with participants, mothers, caregivers, husbands, and clinicians.

We set up a community advisory board of 10 members at each hub. These comprise a pastor, imam, local council representative, facility in charge, a facility midwife, a private clinic representative, a mothers’ representative, father representative, a school teacher, mother-in-law, and elderly woman. These meet quarterly and discuss the project, review study protocol, documents, plans, questionnaire, progress, and interpret study outcomes.

The PPI steering team has established a specific local PPI groups at each hub, namely;Budaka hub: the sick mother/ baby group in the intervention arm,Busiu hub: the sick mother/baby group in the comparator armKolonyi hub: Non-study participants with sick-babies or sick mothers themselves

These serve as local maternal and infant infection support groups in the area. At each time, the composition is about 10 members. These groups provide a forum through which the trial team can engage with users and ensure responsive feedback. The feedback from these groups is communicated to the site trial management team (site TMT), the international trial management group (TMG), and trial steering committee (TSC).

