## Discussion

We are evaluating whether the provision of alcohol-based hand rub (ABHR) to pregnant women for postnatal household use is effective for the prevention of severe illness or death during the first 3 months after birth. To the best of our knowledge, this is the first study that determines the effectiveness of ABHR given to mothers in preventing infant infections. Our intervention has high potential for scale-up as the ABHR can be added to birth kits that are routinely given to pregnant women. Furthermore, ABHR used in this trial was locally manufactured from a sugar processing plant and is therefore financially sustainable. The COVID-19 pandemic normalised the use of ABHR also among persons who previously showed scepticism given the alcoholic nature of the product.

Unlike previous trials in LICs that assessed whether provision of pit-latrines and hand washing facilities reduces infections, our study assessed a more proximal intervention; as the use of ABHR before touching the infant could prevent transfer of infections to the infant whether or not the family has a pit latrine. ABHR potentially reduces the inconveniences encountered in implementing hand hygiene in complex household situations where water is often scarce. Also, in places where hand washing is not feasible, practical or convenient such as funerals, parties, and while travelling, ABHR is preferable.

The large size of the trial reduces the likelihood of a type II error. The main study outcome is validated by a group of three medical doctors (a neonatologist, a paediatrician and a general doctor) and as such the likelihood of measurement bias is reduced. Also, since our definition of sepsis involves hospitalisation or death, which are hard outcomes, we reduce the potential of measurement bias since some of the signs and symptoms of child infections are non-specific.

Regular visits by trained midwives will most likely reduce the incidence of infection and death, due to early detection of poor practices or signs of infection and initiating the necessary referral. Also, the availability of study doctors and medication ensures that participants in the trial get superior care to the rest of the infants. Finally, COVID-19 normalised ABHR use; as such, participants in the control villages could use it as measure against COVID-19. We collect data on its use in both arms and will do a per-protocol analysis to assess this effect.

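### The attempted masking of the research midwives leaves the hand-rub poster uncovered, and because allocation is by village one lapse can expose a whole cluster, so referral and detection could differ by arm in either direction

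*Protocol article*

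**What the plan says.** Under Masking and code breaking, the article states: "Although this is an open-label study, we attempt to mask the research midwives during the follow-up period". It lists four safeguards:

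- Separate teams: "This is achieved by separating the research midwives and the trainers in two separate teams in different locations".
- No discussion: "we ask the study participants not to discuss their hand hygiene methods with the research midwives".
- Hiding: "the mother is asked to keep the ABHR bottles out of sight of the research midwives on the day of the face-to-face visit", with advance notice of each visit so that she can do so.
- The closeout interview, which asks about hand-rub use, is done by the trainer and not by the midwife.

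Other sections bear on how well this can work:

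- Intervention arm, text after Table 1: "A double-sided poster (Appendices 1 and 2) supplements the training, summarising the instructions in both a written and visual format". One side covers antenatal use and the other postnatal use.
- Identification, recruitment, and study procedures: "The same research midwife performs regular telephone calls and personal follow-up visits up to 12 weeks". Midwives or village health team members refer sick infants, and study doctors either treat or transfer them.
- Randomisation: the draw took place before representatives of every village in the area, and its last ball fixed which clusters were intervention. The same paragraph says that the final sequence is kept from the other scientists until the trial ends.
- Participant and public involvement: the Budaka group is "the sick mother/ baby group in the intervention arm" and the Busiu group is its comparator counterpart. Feedback goes to site management, the trial management group and the trial steering committee.
- Discussion: "The main study outcome is validated by a group of three medical doctors (a neonatologist, a paediatrician and a general doctor"; the sepsis definition requires hospitalisation or death.

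**The concern.** Two of the four safeguards depend on each mother's co-operation, and the hiding request names only the hand rub and its bottles. A poster about hand rub in the home identifies the arm as surely as a bottle does. In an individually randomised trial a slip would unmask one infant. Here the village is the unit of allocation, so a slip in one home tells the midwife the arm of every other infant she follows in that village.

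This matters because part of the outcome passes through staff judgement. Death does not depend on who is looking, but admission can follow a referral or transfer decision. Staff who know the arm may refer more readily in one arm than the other, and the difference would be read as an effect of the hand rub. The Discussion credits the three-doctor validation with reducing measurement bias. Validation can reject an event that was reported, but it cannot restore one that was never referred.

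A second point concerns the investigators. The sequence is said to be withheld from the scientists, yet the draw was public, and feedback from groups defined by arm reaches committees on which the chief investigator and study statistician sit.

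**Working it through.** No figure in the document is in dispute, so the check is mainly textual; the arithmetic only shows scale.

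**Text side by side**

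| Route | Safeguard stated |
|---|---|
| Hand rub and bottles in the home | Hiding request |
| Talk about hand hygiene | Request not to discuss |
| Contact with trainers | Separate teams and locations |
| Closeout questions | Asked by the trainer |
| Poster in the home | None stated |
| Village health team members and study doctors, who refer or transfer | None stated |
| Public draw and arm-defined groups, against a withheld sequence | None stated |

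**Step 1. Chance that a cluster is revealed**

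Inputs: 5932 mothers and 72 clusters (Size determination); 5 home visits after birth (Abstract, Methods). The disclosure risk per visit, q, is assumed, with visits taken as independent.

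- Mothers per cluster: 5932/72 = 82.4. Home visits per cluster: 5 × 82.4 = 412.
- P(at least one disclosure) = 1 − (1 − q)^412.
- q = 0.1%: 34%. q = 0.5%: 87%. q = 1%: 98%.

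These are end-of-trial figures. The average share of visits made with knowledge from an earlier visit is 1 − [1 − (1 − q)^412]/(412q), if what one midwife learns counts for the whole cluster:

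- q = 0.1%: 1 − 0.338/0.412 = 18%
- q = 0.5%: 1 − 0.873/2.06 = 58%
- q = 1%: 1 − 0.984/4.12 = 76%

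**Step 2. Lower detection in the intervention arm, no true effect**

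An unpooled two-proportion normal test is used, at two-sided 5% (assumed). Effective n per arm = 2966/[1 + (82.4 − 1) × ICC], which is 2966/1.814 = 1635 at ICC 0.01 and 2966/1.407 = 2108 at ICC 0.005. The event rates and ICCs are among those in Size determination; the detection differences are assumed.

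Example: rate 15%, detection 10% lower. The rates are 0.150 and 0.135, the standard error is √[(0.150 × 0.850 + 0.135 × 0.865)/1635] = 0.0122, and z = 0.015/0.0122 = 1.23. The rejection probability is 23%.

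| Detection lower by | Rate 15%, ICC 0.01 | Rate 5%, ICC 0.005 |
|---|---|---|
| 5% | 9% | 7% |
| 10% | 23% | 12% |
| 15% | 46% | 21% |

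The table supposes that every intervention village is known throughout. Diluting a 10% difference by the shares in Step 1 gives net differences of 1.8%, 5.8% and 7.6%. At rate 15% and ICC 0.01 the rejection rates become about 5.5%, 11% and 15%.

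**Step 3. Higher detection in the intervention arm, true 25% reduction**

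The pilot saw more care-seeking in treatment clusters (The BabyGel pilot trial), so this direction is at least as plausible. With 10% more detection the observed ratio is 0.75 × 1.10 = 0.825, a 17.5% reduction. Power at rate 15% and ICC 0.01 falls from 89% to 59%. With 5% more detection the ratio is 0.7875 and power is 76%.

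**The case against.** The case on the other side is substantial. Masking does not rest on hidden bottles alone: separate teams and the trainer-led closeout are structural, and the closeout is explicitly meant to keep the village allocation from the midwife. The article calls the trial open-label and the masking an attempt, so it does not claim secure masking. The sepsis definition requires hospitalisation or death, partly because some signs of infection are non-specific. Mothers can also ring the hotline or go straight to a facility with free care, so detection does not depend on the midwife alone. Finally, this is a condensed article, and details on the poster or on what the three doctors receive may sit in procedures that are not shown.

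Most of this stands and limits the point. A reader might infer that the arm is in fact revealed, but the text does not show that. It does not say that the poster is displayed on a wall, that midwives attended the draw, or that they meet the patient groups. Repeat visits by one midwife raise exposure but disclose nothing by themselves. A reader might also infer that the three doctors see only cases flagged by midwives; the article does not say so. Nor may the 98% be read as a forecast, since it comes from an assumed rate.

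What the objection does not remove is the gap in the hiding request as written, the reach of one lapse under village allocation, and the fact that admission can follow a staff decision. Events never referred stay beyond the reach of validation.

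**Conclusion.** The point holds as a residual risk of bias that can be reduced cheaply, not as demonstrated unmasking. The hiding request omits the poster, no masking is described for village health team members or study doctors, and the Discussion gives validation more credit than it can earn against missed events. The public draw and the arm-defined groups sit badly with withholding the sequence from the scientists; that is a tension to resolve, not evidence that outcome assessors know the arm.

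The size is unknown, because the documents give no disclosure or detection rates. Under the assumptions shown, a 10% detection difference does little if few villages become known (false-positive rate about 5.5%) and considerable harm if all are known from the start (about 23% at a 15% event rate). In the opposite direction it would mask part of a true effect. Neither direction can be presumed. The change is worth making while recruitment continues.

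**What to change.** 1. Extend the hiding request to the poster and all other hand-rub materials. Alternatively, give control homes a soap-and-water poster in the same format, so that a poster no longer marks the arm.
2. Have the three-doctor group judge all infant deaths and all admissions, drawn from facility and study-doctor records, with village, hub and any mention of hand rub removed. State this in the protocol. It protects classification and catches admissions that midwives did not report, although it still cannot recover illness that never reached a facility.
3. Draw the patient groups at each hub from both arms, and pass their feedback to the trial management group and trial steering committee without arm labels. Reword the statement on withholding the sequence so that it fits a draw held in public.

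Any disclosure or detection rates used to discuss this risk should be labelled as assumptions and shown as a range in both directions.

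Cost: a slightly larger caseload for the three doctors, redaction work, and printing of a control poster if that option is chosen. Nothing changes in the care of the infants.

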### Study assessment visits

Table 1 shows the time schedule for study procedures conducted by research midwives and ABHR trainers.

### Safety reporting

Safety of the women and babies participating in this study is paramount. Although this is not a clinical trial of an investigational medicinal product, safety data on both the women and the babies (including adverse events (AEs) and serious adverse events (SAEs) are collected carefully and reported to the sponsor, local IRB, and the Independent Safety and Data Monitoring Committee (ISDMC). The key participants in this study are the neonates, and adverse events that could be influenced by the trial interventions are outcomes for the study. Data on these events are recorded on the electronic Case Report Forms (CRFs).

### Data management

Data capture is primarily on electronic case report forms that were created using the REDCap software package (Vanderbilt University, USA) on dedicated study tablets. All records are stored and backed-up on a continuous basis on a secure off-site server at LSTM on an encrypted standalone hard drive. The data manager and information systems developer are based in the GHTU and are responsible for management of these data after they are transferred to Liverpool. Three hub data supervisors oversee each of the three study centres (hubs) in Mbale and Budaka, each of whom are responsible for curating data collected at their centre; the team work closely with the GHTU and meet weekly to reconcile any anomalies. The research data will be stored long-term in its original electronic format, both in a unified large database and in a public database containing all data collected during the study except for any information that could identify individual mothers or their babies. The public database will be updated as necessary to achieve long-term preservation (e.g. should software becomes obsolescent). These data will be preserved for 15 years. On the consent form, participants are asked if they agree to the use of their data for future research or studies without notifying them. Participants are also asked for permission for the research team to share relevant data with people from the Universities taking part in the research or from regulatory authorities, where relevant. This trial does not involve collecting biological specimens for storage.

### Statistical methods

#### Size determination

The total sample size for this study is 5932 mothers and their babies (multiple births were considered to be a single birth for this calculation). The sample will be obtained from 72 clusters arranged in 3 geographical areas of 24 clusters. The intra-cluster coefficient (ICC) estimate from the pilot study was 0.17 (95% CI 0 − 0.65); however, a study by Pagel [17] reported ICC estimates from five similar context cluster-randomised trials predominantly in the range 0.01 to 0.10, which is considered more realistic for the proposed study. The sample size calculations are based on a primary endpoint of severe infection, with estimated rates of 5–30%.

The anticipated sample size will have:90% power to detect a reduction in infection rate of ≥ 25% for comparator arm rates down to 15% if ICC ≤ 0.01, or to detect a reduction in infection rate of ≥ 33% for comparator arm rates down to 5% if ICC ≤ 0.001.80% power to detect a reduction in infection rate of ≥ 25% for comparator arm rates down to 10% if ICC ≤ 0.01, or to detect a reduction in infection rate of ≥ 33% for comparator arm rates down to 5% if ICC ≤ 0.005.

In the pilot study, we had a small (2%) loss to follow-up rate. Therefore, only complete cases will be used with no imputation of missing outcomes. No adjustment of sample size is planned for such a small rate of loss to follow-up, but the rate is being monitored by the ISDMC so that the final recruitment time can be extended if needed.

Clusters that reach their planned sample size early will continue to recruit until the study recruitment period is completed. If the planned recruitment size is not achieved by the end of the planned time period, the study may be underpowered, in which case permission will be sought from the management committees and funder to continue recruiting for a longer period to reach the required sample size.

Should it prove impossible to select 72 village clusters that meet the above selection criteria and have a combined estimate of 5932 births over the study period, additional clusters will be recruited into the study as feasible, to achieve the required sample size. If, however, the projected birth rate across the area covered by the three study areas falls below the required level and additional clusters are needed during the study period, the selection of additional clusters will be carried out in conjunction with the ISDMC. To preserve the balance in the two study arms, clusters will be recruited into a study area in pairs; one cluster in each pair will be allocated to the intervention arm and the other in the pair to the control arm.

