#### Statistical analysis plan

As some mothers in clusters randomised to the intervention arm may not use the ABHR provided while others in clusters randomised to the comparator arm may acquire an ABHR for themselves, the primary statistical analysis will be by the principle of “intention-to-treat (ITT)”. That is, all mothers and babies will be analysed in the study group to which their village of residence was randomised; this provide appropriate allowance for non-compliance in both groups and produce estimates of intervention effect that are more reflective of what might occur should the provision of an AHBR to new mothers be adopted as a health policy.

Initially, incidence rates of the primary outcome will be compared across the two study arms using generalised estimating equations (GEEs) to allow for clustering effects. A negative binomial distribution and log link function will be used with outcomes in the same cluster assumed to be equally correlated (exchangeable). Effects sizes will be reported as incidence rate ratios (IRRs) with their 95% confidence intervals calculated using robust Huber-White “sandwich” standard errors to correct for any slight misspecification of the correlation structure. Time to the first occurrence of the primary outcome then be analysed in the same way but using Cox proportional hazards regression model with frailty at village level with mothers/babies lost to follow-up included as censored observations. Intervention effects will be reported as hazard ratios with their (robust) 95% confidence intervals. IRR and hazard ratio estimates will be presented both unadjusted and adjusted for important covariates (including age of mother, sex of infant, study hub/geographical area, WASH status (availability of tapped water and type of latrine in dwelling), rural and peri-urban status, highest education level achieved by mother).

All secondary outcome measures will be assessed also using GEE techniques as for the primary outcome, with appropriate distributional assumptions depending on the statistical nature of each measure. Effect sizes will be presented with their (robust) 95% confidence intervals, both unadjusted and adjusted for important covariates. However, to gain some insight into the possible effect of ABHR if adopted fully, a secondary analysis will be performed on a per protocol principle.

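### The stated power figures are all met only at an unstated one-sided 5% level; at the two-sided 5% implied by the planned 95% intervals, the 80% claim for a 10% comparator rate is about 72%

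*Protocol article*

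**What the plan says.** The Size determination section of the protocol article fixes the design: "The total sample size for this study is 5932 mothers and their babies", and "The sample will be obtained from 72 clusters arranged in 3 geographical areas of 24 clusters". The Randomisation section gives 1:1 allocation by cluster, with 12 clusters per colour in each area: "This process was repeated for the remaining five strata in turn to randomly designate 12 clusters as" red and 12 as yellow.

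Four power statements follow for this one sample size:

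1. "90% power to detect a reduction in infection rate of" at least 25%, "for comparator arm rates down to 15% if ICC" is at most 0.01.
2. Also 90%, for a reduction of at least 33%, "for comparator arm rates down to 5% if ICC" is at most 0.001.
3. 80% for a reduction of at least 25%, "for comparator arm rates down to 10% if ICC" is at most 0.01.
4. 80% for a reduction of at least 33% from the same 5% rate, with ICC at most 0.005.

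The section gives no significance level and does not say whether the test is one- or two-sided. On the analysis, the article says: "Effects sizes will be reported as incidence rate ratios (IRRs) with their 95% confidence intervals". Hazard ratios are also to be given with 95% intervals. One-sided testing is not mentioned anywhere.

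**The concern.** A 95% interval used to judge an effect corresponds to a two-sided 5% test. Power stated for the trial should therefore be power at that level. When the four statements are recomputed there, scenario 3 falls about 8 points short and the two 5% scenarios fall short by smaller amounts.

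The stake is how a null result is read. The Discussion says that the large size lowers the risk of a type II error. In scenario 3 that risk is about 28% (100 − 72), not the 20% that the power statement implies. A reader relying on the stated figures would take a null result as more informative than it is.

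**Working it through.** **Inputs.** From Size determination and Randomisation: 2966 mothers and 36 clusters per arm, and mean cluster size m = 5932/72 = 82.39. Assumptions: equal cluster sizes, no loss to follow-up, the infection rate treated as a proportion, and each ICC at its stated upper limit.

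**Formulas.** Design effect DE = 1 + (m − 1) × ICC. Effective size per arm n_e = 2966/DE. Test statistic z = (p1 − p2)/√[(p1q1 + p2q2)/n_e], with q = 1 − p. Power = Φ(z − 1.96) at two-sided 5%, or Φ(z − 1.645) at one-sided 5%.

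**Scenario 3 in full.** DE = 1 + 81.39 × 0.01 = 1.814, so n_e = 2966/1.814 = 1635. p1q1 + p2q2 = 0.10 × 0.90 + 0.075 × 0.925 = 0.159375. The standard error is √(0.159375/1635) = 0.00987 and z = 0.025/0.00987 = 2.532.

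- One-sided 5%: Φ(2.532 − 1.645) = 81.3%. This reproduces the stated 80% as a minimum.
- Two-sided 5%: Φ(2.532 − 1.960) = 71.6%.

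**All four scenarios** (one-third reduction in brackets):

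| Comparator rate, reduction, ICC | DE | Stated | One-sided 5% | Two-sided 5% |
|---|---|---|---|---|
| 15%, 25%, 0.01 | 1.814 | 90% | 93.8% | 88.9% |
| 5%, 33%, 0.001 | 1.081 | 90% | 92.1% | 86.4% (87.1%) |
| 10%, 25%, 0.01 | 1.814 | 80% | 81.3% | 71.6% |
| 5%, 33%, 0.005 | 1.407 | 80% | 85.0% | 76.4% (77.3%) |

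**Other two-sided methods.** The most favourable standard alternative holds the between-cluster coefficient of variation k constant, with k² = ICC(1 − p1)/p1. The variance of the difference is then [(p1q1 + p2q2)/m + k²(p1² + p2²)]/36. For scenario 3, k = 0.30 and the variance is (0.001934 + 0.001406)/36 = 0.0000928. Then z = 0.025/0.00963 = 2.595 and power is 73.7%. The same method gives 90.4% for scenario 1, 86.7% (87.4%) for scenario 2 and 78.0% (78.9%) for scenario 4. Other choices for scenario 3 go lower: 71.2% on the log risk ratio scale, 70.5% with a t reference on 70 df, 71.1% after 2% loss, and about 70% with an assumed cluster-size CV of 0.3. No two-sided variant tried with the stated size and ICC gives 80%.

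**Scenario 2 with no clustering.** Size per arm for 90% power is (1.960 + 1.2816)² × (p1q1 + p2q2)/(p1 − p2)². For 5% v 3.35% this is 10.507 × 0.079878/0.0165² = 3083; for a one-third reduction it is 3016. The trial has 2966. Power at ICC 0 is 88.9% and 89.5% respectively.

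**ICC limits that would support the stated power at two-sided 5%.** Scenario 3 needs 2001 effective mothers per arm for 80%, so ICC ≤ (2966/2001 − 1)/81.39 ≈ 0.006. Scenario 4 needs 2303, so ICC ≤ (2966/2303 − 1)/81.39 ≈ 0.0035. Scenario 1 needs 1699 for 90%, so ICC ≤ 0.0092, which rounds to the stated 0.01.

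**The case against.** The strongest reply is that the article condenses a fuller protocol and may leave alpha to it. The 95% intervals describe how effects are reported, not how the sample was sized. At one-sided 5% all four statements hold as minimums, which looks like a consistent calculation at an unstated level and not four slips of arithmetic. That account of the source is plausible, and the omission of alpha alone would not be a finding. It does not remove the mismatch: the article never mentions a one-sided level, and power at one-sided 5% is not power for a conclusion drawn from a two-sided 95% interval.

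Three stronger readings are tempting and are not supported.

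- A reader might infer that all four figures are wrong. Scenario 1 is 88.9%, or 90.4% with constant CV, and is approximately met. Scenario 4 is a modest gap of 1 to 4 points.
- A reader might compute that scenario 3 needs about 7260 mothers. That keeps 82 per cluster and so assumes about 88 clusters (7260/82.39). With 72 clusters at ICC 0.01, each would need about 124 mothers, about 8,925 in total. Neither is a recruitment target that the documents support.
- A reader might infer that decisions to extend recruitment rest on these power figures. Size determination ties extension to the planned recruitment size and to loss to follow-up, and ties extra clusters to projected births.

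**Conclusion.** The point holds in limited form. The stated powers are all met only at a one-sided 5% level, which does not match the planned 95% intervals. At two-sided 5%:

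- **10% rate, ICC 0.01:** about 72% (72–74% by the design-effect and constant-CV methods), not 80%. This is the clear error.
- **5% rate, ICC 0.001:** about 86–87%, not 90%, and just under 90% even with no clustering.
- **5% rate, ICC 0.005:** about 76–79%, not 80%.
- **15% rate, ICC 0.01:** about 89–90%, so no material error.

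This rests on reading the 95% intervals as a two-sided 5% criterion, and on equal clusters with no loss. Unequal clusters or loss would lower power further.

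**What to change.** In Size determination, state alpha, sidedness and the cluster-size assumption. Then do one of the following:

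- restate power at two-sided 5%, in the order listed above, as about 89%, 86–87%, 72% and 76–77%; or
- keep the 80% statements with lower ICC limits, about 0.006 for the 10% scenario and about 0.0035 for the second 5% scenario, and withdraw the 90% claim at a 5% rate.

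If the figures were calculated one-sided, say so and give the two-sided figures beside them. This rewords one paragraph and leaves the planned analysis unchanged. The only cost is a less favourable stated power.
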